#### Audiotaping of consultations

SCAs will be asked to audiotape a sample of intervention and control consultations. The tapes will be used to assess the fidelity of the intervention and to describe the content of ‘standard advice’. They will also provide data on the time taken to deliver the intervention and standard advice.

### Randomisation

Participating smokers will be randomised by the iQuit computer program during the consultation such that a particular SCA will see approximately equal numbers of intervention and control participants i.e. individual level randomisation stratified by SCA. The sequence will be generated by a computer-based random number generator using the method of random permuted blocks with block sizes of four and six to make the sequence difficult to predict without leading to a major imbalance in numbers between intervention and control groups if a block is incomplete at the end of recruitment. The allocation sequence will be stored on the web server database prior to the trial start. It will be accessible to the investigators but not to the SCAs or participants. Allocation will be made by the trial web server as soon as Part 1 of the questionnaire has been submitted. At this point, the SCA and the participant will become unblinded to group allocation.

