#### Recruitment: participants

Participants will be recruited by two methods:

1. Opportunistic recruitment. Patients who self-refer, or who are referred via another health professional, to the SCA for smoking cessation advice will be given (or sent via post) a Participant Information Sheet (PIS) and Participant Consent Form (PCF) by the practice reception staff. Posters will be displayed in the practice and study leaflets will be placed in the waiting area to encourage self-referral.

2. Proactive recruitment. Practices will be asked to identify potential participants from smoking status data collected in recent medical appointments. Recent smokers are likely to be current smokers. A list of potential participants will be generated from the practice database by a member of the primary care team. The list will then be pre-screened by a practice clinician for eligibility. A random sample of those eligible to participate will be selected and sent, via post from the GP Practice, a covering letter from patient’s GP providing information as to why they are being written to (‘smoker’ status on practice database), details of smoking cessation advice available to them, a leaflet outlining the study, and a copy of the PIS and PCF.

The consent procedure will follow Good Clinical Practice guidelines [26]. If they have not already done so, those interested in participating in the research will be requested to phone or attend the practice to make an appointment with the SCA. When potential participants attend their initial appointment with the SCA, they should already have received information regarding the trial, as outlined above. This will ensure that participants have had at least 24 hours to consider whether to take part in the study. They will be asked whether they wish to take part in the study, and their eligibility will be checked by the SCA. If they have not received information about the study prior to attending the consultation, they will be given an information pack by the SCA and invited to return at a later date.

Those who do not wish to participate, or who are ineligible, will receive usual care. Screening forms will be completed to record non-personal details of those individuals who are interested in taking part but found to be ineligible.

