#### Training

SCAs will receive training on how to deliver the intervention and the importance of collecting and recording accurate and complete data from all participants. Training will also include other research skills including the taking of informed consent and the issue of confidentiality within a research setting. In a one-to-one session with one of the research team, designed to rehearse what will happen in the consultation with the smoker, SCAs will be trained to use the iQuit computer program by completing the online questionnaire, to follow the research protocol, to complete case report forms, and to use a Smokerlyser (Bedfont) CO monitor and an audio recorder. Follow-up training and ongoing support will also be provided by the research team.

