#### 8-week follow-up

The eight-week follow-up will be via a postal questionnaire sent directly to participants from the study centre. The questionnaire will assess self-reported abstinence and the acceptability and feasibility of the intervention by those participants who received it. Non-responders (those whose questionnaire has not been returned to the study centre within 2 weeks) will be phoned by a research interviewer, initially blinded to the participant’s group allocation (control or intervention). The participant will be given the option of completing the questionnaire over the phone or completing and returning it by post (they will be sent another copy if they need one). For the first option, if the participant is unwilling to complete the full questionnaire over the phone, only the smoking outcome questions will be asked. If it is not possible to contact the participant by telephone after six attempts, no further attempt will be made to collect eight-week follow-up data from that individual; however, they will still be included in the study for follow-up at six months.

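### Investigators can read the whole pre-generated allocation sequence, with no stated need or time limit: a minor, avoidable gap in how upcoming allocations are protected

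*Protocol article*

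**What the plan says.** The Randomisation section describes individual allocation stratified by SCA, using "random permuted blocks with block sizes of four and six to make the sequence difficult to predict". On storage and access it says: "The allocation sequence will be stored on the web server database prior to the trial start", and then "It will be accessible to the investigators but not to the SCAs or participants". It gives no reason for the investigators' access, no end date and no restriction. On release it says: "Allocation will be made by the trial web server as soon as Part 1 of the questionnaire has been submitted".

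Enrolment is done at the practice. Under Recruitment: participants, the SCA has this task at the first appointment: "They will be asked whether they wish to take part in the study, and their eligibility will be checked by the SCA". For proactive recruitment a list is drawn from the practice database, and "The list will then be pre-screened by a practice clinician for eligibility".

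The Training section describes one-to-one training of SCAs by the research team and adds: "Follow-up training and ongoing support will also be provided by the research team".

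Under 8-week follow-up, postal non-responders "will be phoned by a research interviewer, initially blinded" to allocation. The Discussion adds that the primary outcome is asked at the start of that interview. Its own statement on concealment covers SCAs and participants only.

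**The concern.** The access rule is stated outright, so this is not a detail that a condensed article has left out. It lets people on the research side see the next assignment for any given SCA, and nothing described in the article requires that.

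The trial has few other protections. The SCA and the participant know the allocation once it is made. The primary outcome is self-reported without biochemical verification, and the Discussion accepts that this carries a risk of bias when participants know their group. Keeping allocations unknown until a participant is committed is one of the safeguards that remain. The trial varied its block sizes to that end, and open access to the list works against the same aim. If an upcoming allocation reached an SCA, it could affect who is encouraged to enrol or when, and baseline comparability could suffer in a way that no analysis can fully repair.

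**Working it through.** The access rule contains no figure, so the check is to set the relevant statements side by side.

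1. **When the list exists.** It is stored before the trial starts (Randomisation). No end to access is given. Access during recruitment is therefore the natural reading, but it is an inference.

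2. **Who can read it.** Investigators can; SCAs and participants cannot (Randomisation).

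3. **Who needs to read it.** The server allocates after Part 1 of the questionnaire (Randomisation). The text messages are automated (Text messaging). The £5 voucher for intervention participants goes out with the eight-week questionnaire (Procedure: initial consultation), which requires past allocations, not future ones. No described task needs the unused part of the list.

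4. **Who enrols.** The SCA checks eligibility and a practice clinician pre-screens the mailing list (Recruitment: participants). Investigators are given no part in choosing patients. The SCA learns an allocation only after submitting Part 1. Concealment at the point of enrolment therefore holds as written.

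5. **Whether a route exists.** The research team supports SCAs beyond the initial training session (Training), and the list is organised by SCA. A person with access could know the next assignment for the adviser they are speaking to. Harm needs two further steps: disclosure by that person, and action by the SCA.

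6. **Whether interviewer blinding is affected.** The article does not say that interviewers are investigators or that they have access. They are described as initially blinded, they phone only postal non-responders, and they ask the primary outcome first. Postal replies involve no interviewer. Blinding here concerns past allocations, and those are held at the study centre in any case, because the texts and vouchers depend on them.

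7. **Whether any design figure depends on this.** The stated size is 300 per group for 20% versus 30%, 80% power, two-sided alpha 0.05. With pooled variance and no continuity correction:

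 n = [1.96·√(2·0.25·0.75) + 0.8416·√(0.20·0.80 + 0.30·0.70)]² / 0.10² = (1.2002 + 0.5119)² / 0.01 ≈ 293.1, rounded up to 294.

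 Power at 300 per group is 80.9%. The stated figure reproduces, and access to the list does not enter the formula.

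8. **Whether predictability gives a size.** A simulation of random blocks of four and six, guessing the arm that lags so far and tossing a coin at ties, is right 68.0%, 68.5% and 68.9% of the time for 12, 20 and 40 participants per SCA. Someone holding the list is right 100% of the time. The first set of figures is a property of blocking within SCA when past allocations are known, and it would be the same after the fix. The 100% applies to people who do not enrol. Neither figure measures bias.

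**The case against.** The strongest reply is that concealment protects against foreknowledge by those who enrol, and the plan secures exactly that: SCAs are denied the list, and the server releases an assignment only after Part 1. Bias would need an investigator to look up an SCA's next allocation and pass it on, and the SCA to act on it. That would be misconduct, not a fault in the described procedure. The article's claim about concealment is limited to SCAs and participants and agrees with the Randomisation section, so there is no contradiction. Named access roles and audit logs are also details that an article may leave to the full protocol.

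Most of this stands, and it is why the point is minor. It does not remove the point. The article states who has access, and what it states is broader than any task it describes.

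A reader might go further and infer that allocation concealment is already weakened, or that the telephone interviewers are not truly blind. The documents support neither. Concealment at enrolment is intact as described, and nothing gives interviewers the list. The bias that the Discussion does acknowledge, self-report by participants who know their arm, has nothing to do with who can read the sequence.

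**Conclusion.** The point holds as a minor, avoidable weakness. Investigators have unexplained and open-ended access to future allocations, while the research team is in continuing contact with the SCAs who recruit. It is a possible route for disclosure, not a demonstrated failure of concealment or of blinding.

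The conclusion rests on two assumptions: that access runs through recruitment, since no limit is stated, and that some of those with access may be among the staff who support SCAs, which the article neither says nor rules out. No size of bias can be calculated from the document. Sample size, power and alpha do not change.

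**What to change.** Replace the access sentence in the Randomisation section with one to this effect: until recruitment ends, future allocations on the server cannot be read by investigators or by staff who support SCAs; access is limited to an existing programmer or data manager who takes no part in recruitment or SCA support.

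Add to the 8-week follow-up section, and carry over to six months, that telephone interviewers have no access to the sequence, or to arm data before the primary outcome is recorded. At six months, the smoking outcome takes the place of the primary outcome in that sentence.

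The cost is a short change of text and a database permission. The downside is that any check of an allocation must go through the one person with access.

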### Procedure: follow-up

All participants will have a routine NHS follow-up at four weeks from quit date and two research follow-ups, at eight weeks and six months from randomisation date.

#### 4-week follow-up

Before they leave their initial appointment with the SCA, participants will be asked to make a follow-up appointment. This visit will occur approximately four weeks after the participant’s quit date (-3 days or +14 days), as per usual NHS practice for smoking cessation. The SCA will record smoking status and other data collected by the NHS routinely for smoking cessation targets. CO level will also be measured. The SCA will also check contact details for the eight-week and six-month follow-ups.

In some instances, practices may follow-up patients by telephone or by postal questionnaire. The research team will collect data on the type of follow-up conducted at four weeks and any interim follow-ups conducted. If participants do not attend the practice for their scheduled follow-up appointment, SCAs will be encouraged to contact them and invite them to attend on an alternative date. Participants who do not attend a four-week follow-up appointment with the SCA at the practice will still be included in the study for follow-up at eight weeks and six months.

#### 8-week follow-up

The eight-week follow-up will be via a postal questionnaire sent directly to participants from the study centre. The questionnaire will assess self-reported abstinence and the acceptability and feasibility of the intervention by those participants who received it. Non-responders (those whose questionnaire has not been returned to the study centre within 2 weeks) will be phoned by a research interviewer, initially blinded to the participant’s group allocation (control or intervention). The participant will be given the option of completing the questionnaire over the phone or completing and returning it by post (they will be sent another copy if they need one). For the first option, if the participant is unwilling to complete the full questionnaire over the phone, only the smoking outcome questions will be asked. If it is not possible to contact the participant by telephone after six attempts, no further attempt will be made to collect eight-week follow-up data from that individual; however, they will still be included in the study for follow-up at six months.

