### Outcome measures

#### Effectiveness

(i) Primary outcome measure

The primary outcome measure of effectiveness will be self-report of being abstinent from smoking for at least two weeks at eight-week follow-up from randomisation date, as assessed by postal questionnaire or telephone interview.

(ii) Secondary outcome measures

Secondary outcome measures will include:

(a) CO-verified self-report of being abstinent from smoking at four-week follow-up from quit date for at least two weeks, assessed at an appointment with the SCA. (We will use the definition recommended for use by local Stop Smoking Services in England [31]: a CO reading that is assessed 25 to 42 days from quit date and is less than 10 parts per million.)

(b) Self-reported prolonged abstinence (at least 3 months) at six-month follow-up from randomisation date, assessed by postal questionnaire or telephone interview. Because follow up will be conducted by post and/or telephone call with a research interviewer, we do not plan to validate self-reports at six months [32]. Furthermore, it would be difficult to bring participants into the surgery for an additional CO measure at this time point. The main alternative, obtaining saliva samples by post for cotinine assay, has several disadvantages: it may yield a low response rate; measuring cotinine at one time point cannot validate prolonged abstinence; smoking behaviour may change between the questionnaire and receipt of the saliva kit; it is impossible to check whether a returned saliva sample is from a particular participant – samples may be substituted; and a significant proportion of participants may still be using nicotine replacement at follow up.

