#### Acceptability

(i) To the SCAs

SCAs’ evaluation of using the iQuit program, as assessed by postal questionnaire (how easy was it to use; how helpful they found it; how it could be improved; would they continue to use it if it were available).

(ii) To the participants (intervention group only)

(a) Participants’ evaluation of the printed advice report, as assessed by postal questionnaire at eight weeks (whether they kept the report; how much of it they read; how clear, useful and relevant the advice was; what they particularly liked and disliked about the report).

(a) Participants’ evaluation of the text messaging component, as assessed by postal questionnaires at eight weeks and six months (e.g. how useful and relevant they found the messages; whether there were too many or not enough; whether they covered the right topics; how the system could be improved).

(a) Proportions of participants who used the HELP and SLIP features; frequency of use.

(a) Proportion of participants who texted STOP to stop receiving further messages; when they did this (number of days into the program); why they did this (assessed on 6-month follow-up questionnaire).

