### Statistical analysis

An analysis plan will be prepared by the study statistician prior to analysis. The two groups will be compared using chi-squared tests and logistic regression analysis for binary outcome measures, and independent t-tests, analysis of variance and linear regression analysis for continuous measures. All tests will be two-sided using an alpha of 0.05.

The main analyses of quit rates will be conducted on an intention-to-treat basis, making the usual assumption that participants lost to follow up are smoking, although we will also conduct sensitivity analyses using a range of less severe assumptions informed by available baseline and interim data [33]. A further sensitivity analysis will involve estimating the intervention effect allowing for clustering of participant outcomes by household. As the mean cluster size (participants per household) will be close to 1, the results and conclusions are not expected to be materially different from the main analysis. The intra-household correlation coefficient will be estimated in order to inform the design and sample size of any subsequent trial.

Proportions, such as many of the secondary outcomes of acceptability and feasibility, and loss to follow up, will be reported overall and for each arm and compared between arms with a p-value from Fisher’s exact test and a 95% confidence interval calculated by the Clopper-Pearson method. Proportions that are defined in a single arm will be estimated with an exact 95% confidence interval using the binomial distribution.

Additional analyses will include an examination of potential effect modifiers (i.e. was the intervention more effective in particular subgroups of smokers?), predictors of quit attempts and success in quitting, and a comparison of study quit rates with NHS reported rates. The cost of delivering the intervention will be assessed in terms of the average length of the consultation in the two conditions.

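### The eight-week mailing that collects the primary outcome differs by arm in content and in enclosure, and counting the lost as smokers carries any net response gap, of unknown sign, into the primary effect

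*Protocol article*

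**What the plan says.** The primary outcome (Outcome measures, Effectiveness) is "self-report of being abstinent from smoking for at least two weeks at eight-week follow-up from randomisation date, as assessed by postal questionnaire or telephone interview". The 8-week follow-up section describes one postal questionnaire: "The questionnaire will assess self-reported abstinence and the acceptability and feasibility of the intervention by those participants who received it".

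The Acceptability section restricts the participant evaluation items to the intervention group. Two blocks fall at eight weeks: "Participants’ evaluation of the printed advice report, as assessed by postal questionnaire at eight weeks", which extends to "what they particularly liked and disliked about the report", and "Participants’ evaluation of the text messaging component, as assessed by postal questionnaires at eight weeks and six months". The text-message block returns at six months, together with the reason for texting STOP.

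Under Procedure: initial consultation, intervention participants are to receive a £5 voucher for texting costs, enclosed with the eight-week questionnaire. No control equivalent is described, and no voucher is mentioned at six months.

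Anyone who has not returned the form within two weeks is telephoned, with up to six attempts, by an interviewer who is at first blinded. By telephone, "if the participant is unwilling to complete the full questionnaire over the phone, only the smoking outcome questions will be asked". A participant who prefers post may be sent the questionnaire again. Six months follows the same procedure.

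The main analysis of quit rates is by intention to treat, "making the usual assumption that participants lost to follow up are smoking". Sensitivity analyses under milder assumptions are planned, and loss to follow-up is to be compared between arms.

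**The concern.** The way the primary outcome is collected should be the same in both arms. Here it differs twice within one mailing: the intervention arm has additional questions to answer, and it receives money with the form. Either could change how many people reply.

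With missing counted as smoking, response is part of the outcome. A quitter who does not reply is analysed as a smoker. If the two arms end with different proportions of outcomes obtained, some quitters are lost from one arm and not from the other, and the difference appears as a treatment effect or as the loss of one. The trial has almost no spare power, so a moderate net gap would matter.

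The protocol itself foresees that some people will balk at the full questionnaire, yet it gives them a short version by telephone only.

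**Working it through.** **Inputs from the protocol article.** 300 per group, 20% v 30% abstinent at eight weeks, two-sided alpha 0.05, stated power 80% (Sample size, power and precision). Lost counted as smoking (Statistical analysis).

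**Assumed, because the documents give no figures.** The net response gap between arms after the telephone step, and the proportion abstinent among those additionally lost.

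**Step 1: reproduce the stated power.** With a pooled variance under the null, power = Φ[(d − 1.96·SE0)/SE1].
- SE0 = √(2 × 0.25 × 0.75/300) = 0.0354
- SE1 = √((0.20 × 0.80 + 0.30 × 0.70)/300) = 0.0351
- Power = Φ[(0.10 − 1.96 × 0.0354)/0.0351] = 80.9%

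The stated 80% is reproduced.

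**Step 2: net deficit in the intervention arm.** Take 20% and 30% as the rates that would be analysed with equal response, and hold control at 20%. Analysed intervention rate = 30% − (net gap × proportion abstinent among those additionally lost).

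| Net deficit | Abstinent among lost | Points lost | Analysed comparison | Power |
|---|---|---|---|---|
| 2 points | 30% | 0.6 | 20% v 29.4% | 76% |
| 5 points | 30% | 1.5 | 20% v 28.5% | 68% |
| 10 points | 30% | 3.0 | 20% v 27.0% | 52% |
| 2 points | 15% | 0.3 | 20% v 29.7% | 79% |
| 5 points | 15% | 0.75 | 20% v 29.25% | 75% |
| 10 points | 15% | 1.5 | 20% v 28.5% | 68% |

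**Step 3: allow for the telephone step.** Only the gap left after telephoning counts. Suppose a 5-point postal gap, with 30% abstinent among those lost.
- Half recovered by telephone: net 2.5 points, 0.75 points lost, power 75%.
- Three quarters recovered: net 1.25 points, about 0.4 points lost, power 78%.

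**Step 4: the opposite sign.** Suppose the voucher outweighs the extra items and the intervention arm ends with a net surplus.
- Surplus of 2 points at 30%: 20% v 30.6%, power 85%.
- Surplus of 5 points at 30%: 20% v 31.5%, power 90%.
- No true effect (20% in both arms), surplus of 5 points at 20%: 5 × 0.20 = 1 point, so 20% v 21% is analysed. The chance of a significant result in favour of the intervention is then 4.9% against the nominal 2.5%.

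**The case against.** A reader might infer that the longer form must lower response in the intervention arm and so pull the result towards no difference. The documents do not support that. The voucher goes out in the same envelope to the same arm and could as well raise response. What reaches the analysis is the net of the two, and nothing in the article fixes its sign.

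The other side also has these arguments:

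- Every postal non-responder is telephoned and may answer the smoking questions alone, and the Discussion says the primary outcome is asked first in the interview. Someone put off by length, in either arm, therefore has a short route. This stands and limits the size. It does not close the gap: calling stops after six failed attempts, and a person who then opts for post is not described as being offered a short form.
- The gaps in the calculation are assumptions. This stands. They show sensitivity and are not forecasts, and the smaller ones do little harm.
- The questionnaire is not shown, so its length and layout are unknown. This stands in part. That the intervention arm is asked more follows from the text; how much more does not.
- Loss is compared by arm and sensitivity analyses are planned. These can reveal a gap and show its influence. They cannot recover outcomes that were never collected, and the main analysis keeps the missing-as-smoking rule.
- Acceptability is the first objective, and splitting the form puts those data at some risk. This stands and is the real price of the change.

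**Conclusion.** The point holds as a minor, cheap improvement. The eight-week mailing differs by arm in two ways, extra items and a voucher, and the main analysis turns any net response difference into an apparent difference in quitting. Neither the direction nor the size is established. If 30% of those additionally lost were abstinent, a net intervention-arm deficit of 2 to 5 points would take power from 81% to 76% or 68%; at 15% abstinent it would be 79% or 75%. A surplus would move the result the other way.

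At six months the extra items recur and no voucher is described, so the only arm difference stated there is the additional questions. That outcome is meant to inform whether a larger trial follows. Nothing here makes the trial invalid or shows a bias towards no difference.

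**What to change.** - Send both arms an identical short outcome form at eight weeks and at six months, and count the outcome as obtained when that form comes back.
- Put the acceptability items in a separate booklet for the intervention arm.
- Offer the outcome-only form also to non-responders who, when telephoned, choose to reply by post.
- Do not tie the voucher to the outcome mailing in one arm only; for example, send it separately from the outcome form. This belongs with the first change: removing the extra items alone would leave the voucher difference unopposed.

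The cost is printing and some additional postage. The downside is that some intervention participants will return the outcome form without the booklet. The loss of acceptability data cannot be sized from the documents, and it should be weighed because acceptability is a trial objective.
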